### Objectives

- Determination of the possible achievement of primary prevention of Coeliac Disease (CD) and related auto-immune phenomena by favourable early dietary practices in the general population
- Evaluation of the interaction between early dietary history and CD related genetic factors known to us on the prevalence and expression of CD in the general population.

### Description of work

- The study base is defined by a representative, population based sample of children born in 1993 and 1997, 8.000 from each cohort, using the Swedish population register. The study on the first cohort (1993) will be finalized before this project starts. However, the results will be brought into the project. The study on the second cohort (1997) falls within the project.
- All cases of symptomatic CD diagnosed before the age of 12 will be identified through the National Register of CD in Swedish children.
- All children will be invited to a screening for CD at the age of 12 including blood sampling and parental questionnaires (on e.g. early dietary history and autoimmune diseases).
- Blood samples of all children will be analysed for tissue transglutaminase antibodies (TTGA), and when CD is suspected a diagnostic small intestinal mucosa will be evaluated we expect to find double

the number of screening-detected cases in the cohort of 1993 compared to the one of 1997.

- Blood samples from all children with CD (symptomatic and screening-detected), from those with an isolated aberrant TTGA response, and from five population based controls per case (n=1800) will be used for HLA and non-HLA genetic analyses (WP5), and for determination of auto-antibodies.
- Questionnaire data on early dietary history and auto-immune diseases will be compared between the CD cases (symptomatic and screening-detected), and population based controls, as differences between these groups and also between the cohorts of 1993 and 1997 are expected.
- The prevalence of CD, both symptomatic and screening-detected, will be compared between the two birth cohorts, and it will be related to differences in early dietary history and genetics (WP5).

### **Deliverables**

D.4.1. Report on the cohort from the CD epidemic (1993) with respect to prevalence of CD and related autoimmune phenomena, n relation to early dietary history and HLA profile (m 30).

D.4.2. Report on the cohort from the post-epidemic period (1997) with respect to prevalence of CD and related autoimmune phenomena, n relation to early dietary history and HLA profile (month 42).

D.4.3 Report combining the results from the 2 with respect to prevalence of CD and related autoimmune phenomena in relation to early dietary history and HLA and non-HLA genetic profile (month 44).

### **Milestones and expected result**

M3. First year analysis (m 12)

M4. Mid-term analysis (m 24)

M5. Final meeting: presentation of the results (m 60)

This population based study exploring birth cohorts with different early dietary history, and with a follow-up of twelve years, gives an opportunity to determine the late effects of breast-feeding and early gluten exposure involved in the primary prevention of CD.

**Work Package (WP) 5: Genetic studies and risk stratification****Introduction**

There is a strong inherited predisposition to CD susceptibility. Around 90% of CD patients possess the HLA-DQ2 and/or HLA-DQ8 molecules. However, the HLA-DQ2 allele is common in the healthy population, carried by approximately 30% of Caucasians. Therefore, genetic factors outside the HLA region contribute to disease susceptibility or resistance. To date, at least three non-HLA loci have been identified that are likely to contain disease predisposing variants, on chromosome 2q (*CELIAC3* locus), on chromosome 5q (*CELIAC2* locus), and on chromosome 19p (*CELIAC4* locus). For two of these regions the disease-causing genes have been identified: the *CTLA4* gene on 2q and the *XX* gene on 19p. *CTLA4* confers an approximately a 1.5-fold increased risk to CD and gene *XX* a 2.3 fold risk. Eleven genome-wide searches for linkage regions have been performed in CD, as well as numerous region specific linkage studies. Participant 5 is involved in fine-mapping of two additional CD loci on chromosomes 6q21-22 and 9p13, large-scale genetic testing of some 100 functional candidate genes, and a genome-wide genetic association studies. The data generated through these ongoing efforts will benefit this proposal. Therefore, it is expected that in the next few years additional loci/genes will be added to the current list of CD susceptibility genes and these will then also be included without jeopardizing the proposed plan of work and the deliverables.

In this proposal we will study the effect of the currently known genetic risk factors on CD and the early dietary intervention, in two cohorts: a Swedish population-based cohort (a representative sample of approximately 1.800 individuals from a total cohort of 16.000 individuals) and a European-based family cohort (approx. 3.500 individuals). Each individual will be genotyped for the four genes listed above: HLA-DQ, *CTLA4*, *CELIAC2*, *MYO9B*. DNA will be isolated from peripheral blood from all participants according to standard protocols. Genotyping will be performed using 384 single nucleotide polymorphisms (SNP) covering these four regions and analyzed on an Illumina Bead Array system. All samples will be blindly coded to prevent any biases in data-analysis. Appropriate controls will be included to control for genotyping and sample

errors. Statistical analysis will be performed separately for the population-based cohort and the family-based cohort.

*Evaluating HLA and non-HLA susceptibility genes in the family-based cohort*

Since the families will be collected from different geographic areas we can also study if this affects their genetic risk profile. Upon the early dietary intervention study the gluten-treated CD cases (randomized to tolerance induction) will be compared to the placebo-treated CD cases for their genetic profile to identify differences in distribution of the four genetic risk factors in high risk families.

*Evaluating HLA and non-HLA susceptibility genes in the population-based cohort*

The population study encompasses in total 16 000 children divided among the birth cohorts of 1993 and 1997. DNA will be available for all CD cases diagnosed before the age of 12, both symptomatic (expected n= 93) and screening-detected (expected n=69), and a representative sample of five controls per identified CD case. Therefore, this cohort is excellently suitable to properly assess the effect of HLA and non-HLA genes at both the individual and the population level.

Genetic testing for the HLA and non-HLA loci will allow evaluation of these genetic factors in relation to the prevalence and the phenotype (symptomatic/screening-detected) of CD. This will allow us to determine the role of both HLA and non-HLA genes on disease-risk in patients and their possible predictive value in the population. In addition, we can determine if these genes are differentially involved in symptomatic *versus* screening-detected CD subjects. Interestingly, since the 1993 and 1997 birth cohorts experienced different exposure with respect to early feeding we will also be able to assess the effect of genetic risk factors on the effect of different early feeding patterns.

|                                |                |    |   |   |                               |   |   |   |   |    |         |    |    |    |    |    |    |
|--------------------------------|----------------|----|---|---|-------------------------------|---|---|---|---|----|---------|----|----|----|----|----|----|
| Work package number            | 5              |    |   |   | Start date or starting event: |   |   |   |   |    | Month 1 |    |    |    |    |    |    |
| Activity Type                  | RTD/Innovation |    |   |   |                               |   |   |   |   |    |         |    |    |    |    |    |    |
| Participant id                 | 1              | 2  | 3 | 4 | 5                             | 6 | 7 | 8 | 9 | 10 | 11      | 12 | 13 | 14 | 15 | 16 | 17 |
| Person-months per participant: | 0              | 48 | 8 | 0 | 48                            | 0 | 0 | 0 | 0 | 0  | 0       | 0  | 0  | 0  | 0  | 0  | 0  |

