## **Work Package (WP) 4: Population based study exploring birth cohorts with different early dietary history**

### **Introduction**

We will take advantage of the “experiment” in the Swedish population with extensive changes in infant feeding practices within a few years, which resulted in a unique epidemic of symptomatic CD in children below 2 years of age. The incidence rate of symptomatic CD increased four-fold to levels higher than ever previously reported, and after a ten-year period on this high level, suddenly returned back to the previous level. A representative sample of 16.000 Swedish children aged 12 years, 8.000 born during the peak of the epidemic (1993) and 8.000 born after the epidemic (1997), will participate in the study. This study is based on a long-standing collaboration with paediatric units in different parts of Sweden, and also a well-developed collaboration with the school health services.

- Design: prospective population based intervention study with a long-term follow-up
- Study base: the study on the 8.000 children from the epidemic will be done before the project, but the results will be used to be compared with the data from the cohort from the post-epidemic period.
- Invitation to participate: requirement for inclusion is an informed consent from the child and its parents.
- Symptomatic CD cases diagnosed before the age of 12-years will be identified through the National Register of CD in Swedish children.
- Screening for CD: all children will be invited for a blood sample during the school-year 2009-2010 for determination of tissue transglutaminase antibodies type IgA (AtTG), and those with s-IgA-deficiency also for AtTG type IgG. When CD is suspected the child is referred for a diagnostic small bowel biopsy. Biopsies will only be performed when medically indicated, that is: only in these children with CD antibodies in their serum that indicate gluten sensitivity and are highly suspect for active CD, and NOT just for purpose of the study. Such children would undergo a biopsy also in non-study circumstances.

- Double the numbers of screening-detected cases in the epidemic cohort are expected compared to the cases in the post-epidemic cohort.
- HLA and non-HLA genetic characteristics and autoimmune serological markers will be assessed in all the children with CD (symptomatic and screening-detected) and in 5 population based controls per case (n=1800).

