**Description of work**

- Setting up a Biobank with DNA from 1.000 high-risk CD cases and their family members, and in 1800 children from the population cohort (expected 160 CD cases and age and sex matched controls).
- Evaluating the currently known genetic risk factors using high throughput SNP genotyping: the HLA predisposing genes (*DR* and *DQ*), gene *MYO9B* (19p13.1), the *CTLA4* (2q33) gene, and the *CELIAC2* (5q31-q33) locus
- Stratification of subjects in different genetic profile classes and comparing the response to dietary intervention among the classes using logistic regression
- Assess whether if the genetic profiles differ across European CD populations
- Assess whether if the genetic profiles differ between high-risk CD families and population-based CD cases

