## **10. Other issues (optional)**

### **10.1 Gender dimension**

The proposed project agrees with the European policy to integrate the gender dimension in FP6 projects, because:

1. The topic to be studied
2. The participants in the project

*The topic of the project.*

The proposed project involves coeliac disease (CD), a disorder that, as most others with autoimmune character, affects women at least twice as men. Also many of the long-term

complications of CD, such as retarded menarche age, infertility, premature births, early menopause and osteoporosis are disorders concerning directly health women's needs. Identification of early nutrition strategies for primary prevention of CD, which is the aim of the proposed project, may thus contribute to improve the health and quality of life of the European women.

The cohorts of PREVENTCD, i.e. the newborns from high-risk families (WP3) and the population based Swedish birth cohorts with twelve year of follow-up (WP4) should preferably reflect the general population with respect to gender distribution, i.e. about the same numbers of girls and boys. However, the gender difference in CD occurrence with two times as many CD cases among girls compared to boys should be taken into account for in the statistical analyses, by always considering stratifying the analyses and the reporting on results by gender. In addition, the project concerns the role of early dietary history in the development of CD, including the role of breast-feeding, a subject that concerns directly the females as mothers, as it does the subject of early nutrition in general.

*The composition of the participants in the project encourages women's participation in research, since:*

- The leaders of five of the seven work packages (WP) of the project, including the coordinator, are females.
- A substantial number of the participants in the proposed project are women, since they are usually dedicated to some of the key disciplines, such as Paediatrics, Clinical Nutrition, Dietetics, Genetics, Epidemiology and Public Health, necessary to carry out the project.

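### WP5 calls the Swedish genotyping set representative of the 16,000, but its sampling rules make it a nested case-control set with two conflicting control rules; absolute risks and predictive values do not follow from it directly

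*Protocol*

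**What the plan says.** All references are to the protocol.

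- **Description of the set.** Section 7.6, WP5 Introduction: "a Swedish population-based cohort (a representative sample of approximately 1.800 individuals from a total cohort of 16.000 individuals".
- **Who is in it.** The WP4 Introduction specifies all children with CD and genotyping "in 5 population based controls per case (n=1800"). The WP4 description of work adds children with an isolated aberrant transglutaminase antibody response. WP5, under the population-based cohort, includes all cases diagnosed before age 12, "both symptomatic (expected n= 93) and screening-detected (expected n=69"), and "a representative sample of five controls per identified CD case".
- **Control rule stated differently.** The WP5 description of work gives 1,800 children, "expected 160 CD cases and age and sex matched controls".
- **Intended use.** Straight after describing the cases and controls, WP5 says: "Therefore, this cohort is excellently suitable to properly assess the effect of HLA and non-HLA genes at both the individual and the population level". It adds that the work will show the role of the genes and "their possible predictive value in the population".
- **Sex ratio.** Section 10.1 reports "two times as many CD cases among girls compared to boys" and expects about equal numbers of girls and boys in the cohorts.

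**The concern.** Two statements are at fault. First, a set that takes every case and only a fraction of the non-cases cannot represent the cohort, because its share of CD is fixed by the control ratio. Second, controls cannot be both a representative sample of the cohort and matched on sex to cases that are two-thirds girls, when the cohort is about half girls.

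This matters because WP5 rests its population-level and predictive claims on the sampling itself. Anyone who takes *representative* at its word could compute carrier risks, predictive values or auto-antibody frequencies straight from the set. Those figures would depend on the 1:5 ratio rather than on the Swedish population. The control rule also governs how children are drawn, so it has to be settled before drawing; the analysis needs to know which rule was followed.

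**Working it through.** **Inputs from the protocol**
- Expected cases: 93 + 69 = 162 in 16,000 children (WP5). Planned prevalence 162/16,000 = 1.01%.
- First screening round (section 9.3): 7,400 participants, 79 with known CD, 192 with suspect serology, 47 of 55 biopsies confirmed.
- DQ2 and/or DQ8 in about 90% of CD patients; DQ2 in about 30% of Caucasians (WP5 Introduction). The 30% covers DQ2 only and is used here as an assumption for DQ2/DQ8.

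**Step 1: the size of the set.** All cases plus five controls each gives 162 × 6 = 972 (960 with 160 cases). The stated 1,800 is not reproduced. A total of 1,800 at 1:5 needs 1,800/6 = 300 cases; 1,800 controls need 1,800/5 = 360. With 162 cases, 1,800 children means (1,800 − 162)/162 = 10.1 controls per case. The isolated-antibody children do not close the gap. Adding 58 or 160 of them (the 0.4% and 1% groups in section 9.3) gives 1,030 or 1,132; giving them five controls each as well gives 1,320 or 1,932.

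**Step 2: the share of CD.** It is 1/6 = 16.7% in a 1:5 set and 162/1,800 = 9.0% in a set of 1,800. In the cohort it is 1.01% as planned. From the first round it is 79/7,400 + (192/7,400) × (47/55) = 1.07% + 2.22% = 3.3%.

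**Step 3: carrier risk if the set were read as representative.** With *s* the share of CD,

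P(CD | carrier) = 0.90·s / [0.90·s + 0.30·(1 − s)]

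| Basis | s | Carrier risk | 1:5 figure ÷ this |
|---|---|---|---|
| 1:5 set, unweighted | 16.7% | 37.5% | – |
| Cohort, planned prevalence | 1.01% | 2.98% | 12.6 |
| Cohort, first-round prevalence | 3.3% | 9.2% | 4.1 |

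At a round 1% prevalence the ratio is 12.75, hence roughly 4 to 13. A set of 162 in 1,800 gives 22.9%, which is 7.7 times the planned-prevalence value. That set should not be compared with 3.3%, since 3.3% of 16,000 is about 525 cases, not 162. If DQ2/DQ8 carriage were 40% (an assumption), the 1:5 ratios would be about 13.8 and 4.4.

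**Step 4: what survives.** The odds ratio is (0.90 × 0.70)/(0.10 × 0.30) = 21 in the set and in the cohort. The attributable fraction follows from it without weights: 0.90 × (21 − 1)/21 = 0.86.

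**Step 5: recovery of absolute risk.** With random controls each carries weight (16,000 − 162)/810 = 19.55. The weighted carrier risk is 145.8/(145.8 + 243 × 19.55) = 2.98%, the cohort value.

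**Step 6: the effect of matching.** At two girls to one boy, 162 cases are 108 girls and 54 boys, so matched controls are 540 girls and 270 boys. With 8,000 of each sex the weights are (8,000 − 108)/540 = 14.6 and (8,000 − 54)/270 = 29.4, not one common 19.55.

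**The case against.** The strongest reply is that no wrong analysis is fixed. The protocol names no estimator for predictive value, and nowhere says that risk will be read from raw proportions. Cases arise in a counted cohort, through the national register and screening, and WP4 plans to relate cohort prevalence to genetics. The denominators therefore exist, and detailed weighting properly belongs in an analysis plan. This stands. A reader might infer that the project will publish carrier risks inflated 4 to 13 times; the document does not support that.

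Other tempting inferences also fail:
- *No population-level effect can be estimated.* Attributable fractions come from odds ratios and carriage among cases.
- *Sex matching distorts the genetics.* The four loci are autosomal, so genotype frequencies should barely move. The consequence is mainly for auto-antibody frequencies and for the weights.
- *Matching defeats section 10.1.* That section asks that stratification and reporting by gender be considered, which matched controls allow.
- *Deliverable D5.6 is compromised.* Nothing assigns the Swedish predictive value to it.

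The point also lies outside the randomised comparison in WP3. What the objection leaves untouched is the wording: the set is misdescribed, and the two control rules and the two set sizes disagree.

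**Conclusion.** The point holds as an error of description and a contradiction in the sampling rule. The set is a nested case-control sample holding 9% to 17% CD, against about 1% planned, or about 3.3% on first-round figures. Relative measures are sound. Predictive value, absolute carrier risk and auto-antibody frequency in the population need sampling fractions or cohort prevalence, and the WP5 suitability claim passes over this.

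The factor of roughly 4 to 13 is the size of the error if *representative* is taken literally for HLA in a 1:5 set. It assumes 90% carriage in cases and 30% in others. The lower end also extrapolates 55 biopsies to all 192 suspect children, and applies the rate from the epidemic birth cohort to both cohorts, although WP4 expects half as many screening-detected cases in the later one. The correction is worth making because prediction in the population is a stated WP5 aim.

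**What to change.** 1. In the WP5 Introduction, delete *representative* and describe a nested case-control sample: all CD cases, plus controls from the same birth cohorts, with the isolated-antibody children named as a separate group if they are included.
2. Reconcile the two WP5 statements on controls and adopt one rule, random within birth cohort or matched on sex, before controls are drawn.
3. State that predictive values, absolute carrier risks and auto-antibody frequencies use the control sampling fractions (by birth cohort, and by sex if matched) or combine odds ratios with the prevalence in the screened cohort. The detail can go in an analysis plan.
4. Reconcile 1,800 with 162 × 6 = 972, by correcting the total, the control ratio or the expected number of cases.

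The cost is wording, weights computed from counts the project already holds, and slightly wider intervals for the weighted estimates.

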**Objectives**

- Evaluation of the genetic factors known to us on the prevalence and phenotype of coeliac disease (CD) by exploring the genetic loci/regions on chromosomes 6p21 (*HLA*), 5q31-q33 (*CELIAC2*), 2q33 (*CTLA4*), 19p13 (*MYO9B*) in both a population-based and a high risk family-based cohort.
- Analysis of the effect of the currently known genetic factors on the response to early dietary intervention in a population-based CD cohort and in a high risk family-based CD cohort

**Description of work**

- Setting up a Biobank with DNA from 1.000 high-risk CD cases and their family members, and in 1800 children from the population cohort (expected 160 CD cases and age and sex matched controls).
- Evaluating the currently known genetic risk factors using high throughput SNP genotyping: the HLA predisposing genes (*DR* and *DQ*), gene *MYO9B* (19p13.1), the *CTLA4* (2q33) gene, and the *CELIAC2* (5q31-q33) locus
- Stratification of subjects in different genetic profile classes and comparing the response to dietary intervention among the classes using logistic regression
- Assess whether if the genetic profiles differ across European CD populations
- Assess whether if the genetic profiles differ between high-risk CD families and population-based CD cases

**Deliverables**

- D.5.1. Single nucleotide polymorphisms (SNP) to capture the genetic variation for the four genetic loci (m6)
- D.5.2. Database to store patient and genotype information (m6)
- D.5.3 6-months updates on the collection of DNA samples for the biobank
- D.5.4. Biobank containing DNA from the population-based cohort study and the family-based cohort study (approx. 4.000 samples) (m38)
- D.5.5 Full genotype data for *HLA*, gene *MYO9B*, *CTLA4*, and the *CELIAC2* locus in CD cases and in the controls (m38)
- D.5.6 Genetic risk profiles and distribution of CD across Europe (m48)

